Hydroxychloroquine (Plaquenil®) 200 mg one tablet daily. See also risk-benefit for the individuals (4.2).

- **Administration follow-up of the medication:**

The responsible physicians for the patients will prescribe the study medication to the patients. In case of an adverse event, the study personnel will contact the sponsor. The sponsor will determine whether the event qualifies to immediate reporting to the regulatory authorities (SUSARs) or will be included to the annual development safety update report to Regulatory Authority (SAE). SAEs occurring after trial termination must be reported if considered related to the treatment during the trial.

- **Concomitant Medications**

The prohibited medication are considered at the time of inclusion (see section 10.2.2 “Exclusion Criteria”) and prevent the inclusion of patient not compliant to inclusion/exclusion criteria due to such ongoing medication.

During the study, all concomitant medications taken in both groups studied will be recorded in the patient record according to standard practice. In case a prohibited medication is noticed it results to patient withdrawal from the study (see sections 11. “Treatment within the Study” and 12. “Withdrawal Criteria and Early Termination”).

- **Adverse Event and Serious Adverse Event Collection, Recording and Reporting**

Known complications of RA and SLE will not be considered as a AE/SAE.

The investigator is responsible for detection and documentation of events meeting the criteria and definition of an adverse event (AE) or serious adverse event (SAE), as provided in this protocol. During the trial when there is a safety evaluation, the investigator or site staff will be responsible for reporting AEs and SAEs, as detailed in this section of the protocol. Clinically significant AEs considered by the investigator to be related to treatment will be followed until resolved or considered stable. It will be left to the investigator’s clinical judgment to determine whether an AE is related and of sufficient severity to require the subject’s removal from treatment or from the trial. A subject may also voluntarily withdraw from treatment due to what he or she perceives as an intolerable AE. If either of these situations arises, the subject should be strongly encouraged to undergo an end of trial assessment and be under medical supervision until symptoms cease or the condition becomes stable.

- **Definition of Adverse Events and Serious Adverse Events**

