- **Definition of an Adverse Event**

An AE is defined as any untoward medical occurrence in a clinical trial subject administered a medicinal product and which does not necessarily have a causal relationship with this treatment. An AE can therefore be any unfavorable and unintended sign (including an abnormal laboratory finding), symptom, or disease (new or exacerbated) temporally associated with the use of a medicinal product, whether or not considered related to the product. For marketed medicinal products, this also includes failure to produce expected benefits (i.e. lack of efficacy), abuse or misuse.

- **Definition of a Serious Adverse Event**

A SAE is defined as any untoward medical occurrence or effect, that at any dose:

- Results in death
- Is life threatening
- Requires hospitalization or prolongation of existing hospitalization
- Results in persistent or significant disability or incapacity
- Is a congenital anomaly or a birth defect
- Is an other significant medical hazard

An AE necessitating hospitalization meets the regulatory definition for “serious” if the inpatient hospital admission includes a minimum of an overnight stay in a health care facility. Any AE that does not meet one of the definitions of serious (e.g. an AE requiring an emergency room visit, outpatient surgery or requires urgent investigation) may be considered by the investigator to meet the “other significant medical hazard” criterion for classification as a SAE. Examples include allergic bronchospasm, convulsions and blood dyscrasias.

- **Definition of a Suspected Unexpected Serious Adverse Reaction**

A SUSAR is both unexpected (not consistent with the applicable product safety reference information) and also meets the definition of a Serious Adverse Event/Reaction. The causal relationship with the treatment is defined as possible by the investigator.

For the purpose of this trial, the reference safety information defining what is to be considered as SUSAR is the Summary of Product Characteristics of Plaquenil (attachment 2).

- **Disease-Related Events and/or Disease-Related Outcomes Not Qualifying as AEs/SAEs**

Expected signs of disease activity such as joint stiffness and joint pain in RA and SLE or exantema in SLE that are well defined as disease related and do not qualify as AEs/SAEs.

- **Clinical Laboratory Abnormalities and Other Abnormal Assessments as AEs and SAEs**

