Abnormal laboratory findings (e.g. clinical chemistry, hematology and urinalysis) or other abnormal assessments that are judged by the investigator as clinically significant will be recorded as AEs or SAEs if they meet the definition of an AE or SAE. Clinically significant abnormal laboratory findings or other abnormal assessments that are detected during the trial or are present at baseline and significantly worsen following the start of the trial will be reported as AEs or SAEs. However, clinically significant abnormal laboratory findings or other abnormal assessments that are associated with the disease being studied, unless judged by the investigator as more severe than expected for the subject’s condition, or that are present or detected at the start of the trial and do not worsen, will not be reported as AEs or SAEs.

The investigator will exercise his or her medical and scientific judgment in deciding whether an abnormal laboratory finding or other abnormal assessment is clinically significant.

- **Reporting of Adverse Events**

The investigator is responsible for ensuring that all AEs (as defined in Section 11.1) observed by the investigator or reported by subjects are properly captured in the subjects’ medical record. In addition, the investigator is responsible for ensuring that all AEs captured on the subjects’ medical records are reported on the CRF. If a subject is permanently withdrawn from the trial because of an SAE, this information must be included in the initial or follow-up SAE report form, as well as the End-of-Trial form. In case of withdrawal due to an AE, then the AE report form and as well as the End of Trial form will be completed. AEs either reported by the patient or observed by the investigator should be described in the following manner:

- The nature of the event will be described in precise, standard medical terminology (i.e. not necessarily the exact words used by the patient). If known, a specific diagnosis should be stated.
- The intensity of the AE will be described in terms of **mild, moderate or severe** according to the investigator’s clinical judgment. The intensity must be independent of the assessment of the seriousness of the AE.

**Mild:** Transient symptoms, no interference with the subject’s daily activities, acceptable.

**Moderate:** Marked symptoms, moderate interference with the subject’s daily activities but still acceptable.

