**Severe:** Considerable interference with the subject’s daily activities, unacceptable.

The duration of the event will be described by the start date and end date.

**Related**: Related AEs or SAEs are classified as adverse reaction (AR) or serious adverse reaction (SAR).

**Probable**: Good reason and sufficient documentation to assume a causal relationship between prescribed medication and the AE. Probable related AEs or SAEs are classified as adverse reaction AR or SAR.

**Possible**: A causal relationship is likely and cannot be excluded. Possible related AEs or SAEs are classified as AR or SAR.

**Unlikely**: The event is most likely related to etiology other than any of the study drugs.

**Unknown**: Impossible to assess e.g. because of insufficient evidence, conflicting data or poor documentation.

**Not related**: No relationship to any of the study drugs.

The outcome of the event will be described in terms of:

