**Recovered/resolved**

**Recovering/resolving**

**Not recovered/not resolved**

**Recovered/resolved with sequelae**

**Fatal**

**Unknown**

- **Time Period, and Frequency of Detecting AEs and SAEs/SUSARs**

From the time a patient consents to participate in the trial until he/she has completed the trial (without any follow up period), all AEs will be reported in the CRF. All SAEs will be reported promptly to *the sponsor*. SAEs will be reported by filling out and sending the SAE form within 24 hours to *the monitor* once the investigator determines that the event meets the protocol definition of an SAE. *The sponsor* will determine whether to whether the immediate notification to the regulatory authorities is required. SAEs occurring after trial termination must be reported if considered related to the treatment during the trial.

After the initial SAE report the investigator is required, proactively, to provide further information regarding the patient’s condition. All follow-up information must be forwarded to *the sponsor and monitor* as it becomes available. The investigator must follow-up all patients with SAEs until the event has subsided (or disappeared), the condition has stabilized, the event is otherwise explained or the patient is lost to follow-up.

For all deaths reported at any time, available autopsy reports and relevant medical reports should be forwarded to *the sponsor*.

Information about a suspected unexpected serious adverse reaction (SUSAR) which occurs during the course of the trial and is fatal or life-threatening will be reported *by the sponsor* as soon as possible to the regulatory authority (directly, and via them to EudraVigilance Clinical Trials Module) and the relevant ethics committee.

This will be done no later than 7 days after *the investigator* first became aware of the reaction. Any additional relevant information should be sent within 8 days of the initial report. A SUSAR, which is not fatal or life threatening will be reported by *the sponsor* as soon as possible, and no later than 15 days after becoming aware of the reaction to the competent authorities (directly, and via them to EudraVigilance Clinical Trials Module) and the relevant ethics committee.

- **Pregnancies and Breast Feeding**

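### The opening sentence of Section 15 exempts disease complications from AE/SAE status without limit, more widely than 15.1.4 and without the severity exception of 15.1.5

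*Protocol*

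**What the plan says.** The protocol addresses disease-related events in three places within Section 15.

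- The opening sentence of the section: "Known complications of RA and SLE will not be considered as a AE/SAE". It has no qualifier, and the protocol does not define which complications count as known.
- Section 15.1.4 exempts expected signs of disease activity. Its examples are joint stiffness and joint pain in both diseases, and "exantema in SLE that are well defined as disease related and do not qualify as AEs/SAEs".
- Section 15.1.5 exempts clinically significant abnormal laboratory findings or other assessments "that are associated with the disease being studied, unless judged by the investigator as more severe than expected" for the patient's condition. Findings present at the start that do not worsen are also exempt.

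The general definitions are broad. Under 15.1.1 an AE includes "disease (new or exacerbated) temporally associated with the use of a medicinal product, whether or not considered related to the product". Section 15.1.2 defines an SAE by outcome, such as death or hospitalization, and makes no exception for the underlying disease.

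The reporting steps follow. Section 15.2 makes the investigator responsible for seeing that AEs captured in the subjects' "medical records are reported on the CRF". In its causality scale, "Possible related AEs or SAEs are classified as AR or SAR". Under 15.3 the SAE form is sent within 24 hours "once the investigator determines that the event meets the protocol definition of an SAE". Section 15.1.3 requires a SUSAR to meet the serious-event definition as well as being unexpected. Adverse events are part of the secondary objective (6.2) and are listed as a secondary endpoint (7.2).

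**The concern.** A disease exemption is safe only if it is limited to events that are expected, ordinary in severity and not plausibly due to the drug. The opening sentence states none of these limits, and it stands ahead of the narrower rules. If a site applies it as written, the decision that an event is a complication of RA or SLE comes before anyone grades causality, and it ends the process.

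That matters here because some reactions that the protocol attributes to HCQ look like lupus. The trial is also open label, so the investigator deciding between disease and drug knows whether the patient is taking HCQ. At stake are the flow of serious events to the sponsor and authorities, and the completeness of a secondary endpoint.

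**Working it through.** No arithmetic applies and the plan gives no figure to reproduce. The check compares the rules, then follows what depends on them.

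**Step 1: scope of the three exemptions.**

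| Rule | What it exempts | Limit on expectedness or severity | Limit for seriousness | Limit for possible HCQ cause |
|---|---|---|---|---|
| Section 15, opening | Any known complication of RA or SLE | None | None | None |
| 15.1.4 | Expected signs of disease activity | Must be expected | None stated | Only indirectly: must be clearly disease related |
| 15.1.5 | Disease-associated abnormal findings and assessments | Reportable if worse than expected | None stated | None stated |

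The first row is the widest in every column. The only explicit severity exception is in 15.1.5, and it covers laboratory findings and other abnormal assessments, not clinical events in general.

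**Step 2: is there a rule of precedence?** None was found. The opening sentence does not refer to 15.1.4, and 15.1.4 does not refer back. Section 15.2 sends the reader to Section 11.1 for the AE definition, but Section 11 concerns treatment and the contents list shows no 11.1, so that reference does not help.

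**Step 3: what depends on AE/SAE status?**

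- Contact with the sponsor (14.2) starts from an adverse event.
- Transfer from the medical record to the CRF (15.2) is required for AEs.
- Causality classes (15.2) are assigned to AEs and SAEs.
- The 24-hour form (15.3) needs an event that meets the SAE definition.
- SUSAR assessment (15.1.3) needs an event that is already serious by definition.

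An event removed by the opening sentence enters none of these steps.

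**Step 4: can drug reactions be read as disease?** Section 8.2 names skin rashes, anemia, visual change or loss and psychosis among HCQ reactions. Section 9, describing SLEDAI-2k, names skin, hematological, visual and neuropsychiatric items among the manifestations of SLE. Reading each pair as an SLE complication gives:

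- *Psychosis or visual change.* Exempt under the opening sentence. Under 15.1.4 the answer depends on whether the investigator regards it as expected and clearly due to lupus.
- *Anemia.* Exempt under the opening sentence. Under 15.1.5 it is reportable if clinically significant and worse than expected for the patient; if it is not worse than expected, both rules exempt it.
- *Rash.* Exempt under the opening sentence. Section 15.1.4 names exanthema in SLE as an example and has no explicit exception for a possible drug cause, so tying the opening sentence to 15.1.4 alone would not settle this case.

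**Step 5: is the event captured as disease activity instead?** Attachment 1 schedules SLEDAI-2k and DAS28 at screening only. Adverse-event enquiry is scheduled at weeks 4, 8 and 12, but what is entered from it depends on the definitions above.

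**The case against.** Excluding disease-related events is a legitimate device, and 15.1.4 can be read as giving the opening sentence its content. The sentence after the opening one also refers to the definitions provided in the protocol. This is a sensible reading, but nothing in the text requires it, and a site that applies the opening sentence literally is also following the protocol.

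Several stronger readings are tempting, and the documents do not support them.

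- *The sentence flatly contradicts 15.1.1.* Any disease exemption departs from the general AE definition, and 15.1.4 does so too. The fault is the unlimited width of the opening sentence and its lack of reconciliation with 15.1.4 and 15.1.5.
- *It contradicts 15.1.2.* That section says "Examples include allergic bronchospasm, convulsions and blood dyscrasias", and a reader might set this against the SLE manifestations in Section 9. But those examples illustrate what an investigator may classify as serious, and the protocol never calls them complications of RA or SLE. SLEDAI-2k headings describe disease activity and are not a list of known complications.
- *The overlap can be counted.* A tally of matching entries depends on how broad headings are paired. Saying how many would change status would treat the examples in 15.1.4 as a closed list, which they are not. The examples are also all on the SLE side; no comparable list exists for RA.
- *Exempted events disappear.* They may still surface. The hospital record documents medically relevant activity (17.2), an external monitor has access to relevant documents (17.3), concomitant medication is recorded (14.3), CRP is measured throughout, and a change in glucocorticoids or NSAIDs is a ground for discontinuation (12). None of these produces a causality grade or an SAE form.

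Exposure is limited as well. Entry requires low to medium disease activity and excludes impaired vision, cardiomyopathy and severe psychiatric conditions, and treatment is 200 mg daily for 8 weeks. This lowers the likely number of events; it does not repair the rule.

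**Conclusion.** The point holds as a wording defect with a safety consequence. The opening sentence of Section 15 is wider than 15.1.4, lacks the severity exception in 15.1.5, and no text subordinates it to either. Followed literally, it lets a serious or possibly HCQ-caused event leave the process before CRF entry, causality grading, the 24-hour form and SUSAR assessment, and it undercounts the adverse-event endpoint where drug and disease effects look alike.

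The size cannot be put as a rate. The protocol gives no event frequencies for the 48 planned patients, and no overlap count is claimed. The conclusion assumes only that some site applies the sentence as written and that an investigator may read such an event as a complication of RA or SLE. The primary lipid endpoint is not affected. The change should be made, chiefly because it costs little and the reporting steps all rest on this definition.

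**What to change.** Delete the opening sentence of Section 15 and put a reference to 15.1.4 in its place, so that one rule governs disease-related events. Add to 15.1.4:

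> Any disease-related event that is serious, more severe than expected for the patient, or possibly related to HCQ is recorded and reported as an AE/SAE.

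Both parts are needed, because 15.1.4 itself has no explicit exception for serious or possibly drug-related events.

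This is an amendment of wording only, with no new visit, test or committee. The cost is some additional AE entries, and possibly SAE forms, that turn out to reflect background disease. In particular, because rash is a listed HCQ reaction, much exanthema arising on treatment would become reportable although 15.1.4 now exempts it. That is a real narrowing of the existing exemption and should be accepted knowingly.

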**Recovered/resolved**

**Recovering/resolving**

**Not recovered/not resolved**

**Recovered/resolved with sequelae**

**Fatal**

**Unknown**

- **Time Period, and Frequency of Detecting AEs and SAEs/SUSARs**

From the time a patient consents to participate in the trial until he/she has completed the trial (without any follow up period), all AEs will be reported in the CRF. All SAEs will be reported promptly to *the sponsor*. SAEs will be reported by filling out and sending the SAE form within 24 hours to *the monitor* once the investigator determines that the event meets the protocol definition of an SAE. *The sponsor* will determine whether to whether the immediate notification to the regulatory authorities is required. SAEs occurring after trial termination must be reported if considered related to the treatment during the trial.

After the initial SAE report the investigator is required, proactively, to provide further information regarding the patient’s condition. All follow-up information must be forwarded to *the sponsor and monitor* as it becomes available. The investigator must follow-up all patients with SAEs until the event has subsided (or disappeared), the condition has stabilized, the event is otherwise explained or the patient is lost to follow-up.

For all deaths reported at any time, available autopsy reports and relevant medical reports should be forwarded to *the sponsor*.

Information about a suspected unexpected serious adverse reaction (SUSAR) which occurs during the course of the trial and is fatal or life-threatening will be reported *by the sponsor* as soon as possible to the regulatory authority (directly, and via them to EudraVigilance Clinical Trials Module) and the relevant ethics committee.

This will be done no later than 7 days after *the investigator* first became aware of the reaction. Any additional relevant information should be sent within 8 days of the initial report. A SUSAR, which is not fatal or life threatening will be reported by *the sponsor* as soon as possible, and no later than 15 days after becoming aware of the reaction to the competent authorities (directly, and via them to EudraVigilance Clinical Trials Module) and the relevant ethics committee.

- **Pregnancies and Breast Feeding**

Subjects who become pregnant during the trial must be withdrawn. The subject will be asked to attend follow-up visits and the outcome of the pregnancy will be followed including reporting on the state of the child 8 to 12 weeks after delivery. Patients receiving treatment shall not breast feed their children.

- **Data Analysis and Statistical Considerations**
- **Sample Size Considerations**

Twenty patients in each group are needed for a 80%-ig power of lowering blood-pressure 10 mmHg. Lowering LDL or TC 0.65 mmol/L with SD 0.7 gives a power of 0.816 when 20 pati-ents in each group are included.

- **Data Sets and Populations**

All subjects enrolled will constitute the analysis population.

- **Interim Analysis**

No interim analysis will be performed

- **Key Elements of Analysis Plan**

Non-parametric tests will be used. Mann-Whitney´s test; when comparison between groups. Statistical testing of multiple assessments over time; Kruskal-Wallis or Friedmans test and Wilcoxons test.

- **Study Administration**
- **Procedure for obtaining informed consent**

Eligible individuals in the study will be contacted by mail containing information about the study, informed consent and return envelope.

- **Definition of Source Data**

All completed assessment scales will be collected in patient specific binders and regarded as source data. All patient related activities of medical relevance will also be documented in the patient hospital record

- **Quality Control**

The trial will be monitored consistent with the demands of the trial and site activity to verify that the:

- Safety and rights of subjects are being protected
- Data are authentic, accurate, and complete
- Trial is conducted in accordance with the currently approved protocol and any other trial agreements, GCP and all applicable regulatory requirements. The investigator and the head of the medical institution (where applicable) agrees to allow *the monitor* direct access to all relevant documents.

An external monitor for the study, not involved in any aspect of the treatment of the individuals participating in the study, will be appointed. The monitor will be appropriately trained, and has the scientific and/or clinical knowledge needed to monitor the trial adequately.

The monitoring will take place in accordance to GCP before, during and after the trial. If any misconduct or neglect would be notified the sponsor and investigator will be notified for to corrective and preventive actions.

- **Quality Assurance**

It is the investigator´s responsibility:

- That he CRFs are reviewed for completeness and accuracy and the appropriate CRF pages also are signed and dated.
- To ensure compliance with GCP and all applicable regulatory requirements, regulatory agencies may conduct a regulatory inspection of this trial. Such audits/inspections can occur at any time during or after completion of the trial. If an audit or inspection occurs, the investigator and institution agree to allow the audit/inspection.
- **Study Closure**

The study will be formally closed when after 12 weeks from study start.

The investigator is fully responsible to consciously monitor safety and make any decisions regarding premature closure of the study because of safety issues

- **Records Retention**

The individuals participating in the study will be coded as serial numbers which means that when summarizing the data, it will not be possible to see which results belong to which individual without access to the coded list with serial numbers. The results will be presented at group level without tracing to the respective individual. The case record files will be stored in locked facilities at the Rheumatology department, Östersund Hospital, Sweden. The randomization will be conducted by study nurses at Östersund Hospital, Rheumatology Unit, not otherwise involved in conduction of this study.

Following closure of the study, the investigator or the head of the medical institution (where applicable) must maintain all site study records, except for those required by local regulations to be maintained by someone else, in a safe and secure location. The records must be maintained to allow easy and timely retrieval, when needed and, whenever feasible, to allow any subsequent review of data in conjunction with assessment of the facility, supporting systems and staff.

The archiving time for the study documents is at least 10 years after the trial has been completed and the study report compiled.

- **Case Report Forms**

A simplified CRF for each participating subject will be manufactured by the investigator and collected in patient specific binders.

- **Rules for completing CRFs**

Use a blackpoint or bluepoint pen when completing the CRFs. Ensure that all relevant questions are answered and that no empty answer fields exist after each visit.

If a test/assessment has not been done and will not be available a straight line should be drawn across the question module and write ‘ND’ (Not Done). If the question is irrelevant indicate this by writing ‘NA’ (Not Applicable). If a value or variable is not known it will be indicated ‘NK’ (Not Known)

The study personnel must ensure that all information entered into the CRF is consistent with the source data.

- **Corrections to CRFs**

Corrections are done by drawing a straight line through the incorrect data. Write the correct data next to the one that had been crossed out. Confirm the correction by writing your initials and the date the correction was done.

If a correction need to be done after the original CRF had been removed and sent to data management, the correction is done by using a Query Resolution Form. This form can be sent by data management when any entered information need to be clarified or when information is missing.

- **CRF flow**

The study personnel are responsible to complete the CRF after each subject visit.

- **Ethical and legal aspects**
- **Study ethics**

This study will be conducted in compliance with the ethical principles that have their origins in the Declaration of Helsinki, Good Clinical Practice, applicable regulatory requirements and this protocol.

- **Study approval, amendments and reporting to authorities**

The study must not start before written approvals by the Ethical Committee and Competent Authority has been obtained.

Changes to the approved final study protocol will be documented in written and numbered Protocol Amendments. The amendments should be signed and dated by the same parties who signed the final protocol, as applicable. All essential changed has to be approved by the Ethical Committee and Competent Authority.

An annual development safety update report (DSUR) will be sent to regulatory authority. Declaration of End of Trial Notification will send by sponsor to regulatory authority within 90 days after end of study.

- **Data Management**

Statistical analyses (see 6.1) will be performed by the investigators.

- **Finance and Insurance**

The study is not sponsored by any pharmaceutical company but financed by research grants.

Every subject participating in the study is covered by his or her national insurance as a patient (Patienskadeförsäkring, Läkemedelsförsäkring).

- **Reference**
